## 7.8 Causality

For all, the investigator will assess the causal relationship between the IMP and the AE using his/her clinical expertise and judgment according to the following algorithm that best fits the circumstances of the AE:

### **Unrelated**

- May or may not follow a reasonable temporal sequence from administration of the IMP
- Is biologically implausible and does not follow known response pattern to the suspect IMP (if response pattern is previously known)
- can be explained by the known characteristics of the subject's clinical state or other modes of medication administered to the subject.

### **Unlikely**

- There is a reasonable temporal relation between the AE and the IMP, but there is a plausible other explanation for the occurrence of the AE possibly.
- Follows a reasonable temporal sequence from administration of the IMP. The AE may equally be explained by the study subject's clinically state, environmental or toxic factors, or concomitant therapy administered to the study subject.
- The relationship between the medical device and AE may also be clinically plausible.

### **Probably**

- Follows a reasonable temporal sequence from administration of the IMP, and plausible reasons point to a causal relation with the IMP.

### **Related**

- Follows a reasonable temporal sequence form administration of the medical device.
- Follows a known response pattern to the medical device (if response pattern is previously known).
- No other reasonable cause is present.

### **Not assessable**

- The causal relationship between the IMP and the AE cannot be judged.

## 7.9 Reporting Procedures

### 7.9.1 Reporting Procedures for Adverse Events (AEs)

A special section is designated to adverse events in the CRF where the following details must be entered:

- type of adverse event (diagnosis or syndrome; if not known signs or symptoms)

- start (date)
- end (date)
- severity (mild, moderate, severe, life-threatening/disabling, death)
- serious (no / yes)
- unexpected (no / yes)
- outcome (resolved, ongoing, ongoing – improved, ongoing – worsening)
- action taken (none, study medication dose reduced, study medication interrupted, study medication discontinued, medication therapy, surgical procedure, hospitalization, other)
- relation to study drug (possibly, probably or definitely related or unlikely, probably not related or definitely not related)

Certain events require immediate reporting to allow the sponsor to take appropriate measures to address potential new risks in a clinical trial. The investigator must report such events to the sponsor immediately; The reporting has to take place within 24 hours after notification. Regardless of relationship to study drug the investigator has to follow within 24 hours of notification:

- Serious adverse events
- Pregnancies

The investigator has to report immediately new significant follow-up information resulting from follow up examination to the sponsor (i.e. no more than 24 hours after becoming aware of the information). New significant information includes the following:

- new signs or symptoms or a change diagnosis
- new significant new diagnostic test results
- change in causality based on new information
- change in the event's outcome, including recovery
- additional narrative information on the clinical course of the event

Investigators must also comply with local requirements for reporting SAEs to the local health authority and IRB/EC

### 7.9.2 Reporting Procedures for SAEs and SUSARs

Investigators be asked to determine for possible AEs. All AEs, whether reported by the patient or noted by study personnel, will be recorded in the patient's medical record and on the Adverse Event eCRF.

**After informed consent** has been obtained but prior to initiation of the study drug, only SAEs considered to be related to a protocol-mandated intervention should be reported (e.g. SAEs related to invasive procedures such as biopsies).

**After initiation of study drug**, all AEs and SAEs regardless of relationship to the study drug will be reported until 7 days or until the event has resolved to baseline grade or better the event is assessed as stable by the investigator the patient is lost to follow-up or the patient withdraws consent.

After 8 days, investigators should report any deaths, SAEs, or other AEs of concern that are believed to be related to prior treatment with the study drug.

Any Serious Adverse Event (SAE) that is ongoing at the time of 7 days should be followed-up until resolved.

In the case of a serious adverse event, the investigator has to use all supportive measures for best patient treatment. The SAE form must be completed by the investigator and reported no more than 24 hours after awareness of the event.

The following details should be available with the initial report:

- patient number
- patient: date of birth, sex
- name of investigator and trial site
- period of administration
- the suspected investigational medicinal product (IMP)
- the adverse event assessed as serious
- concomitant disease and medication
- relevant medical history
- short description of the event and outcome
- description
  - onset and end (if applicable)
  - therapeutic intervention
  - causal relationship to each of the (study drugs)
  - hospitalization or prolongation of hospitalization
  - death, life-threatening, persistent or significant disability or incapacity

If applicable, the initial report should be followed by the follow-up report, indicating the outcome of the SAE.

For SAEs, SUSARs and pregnancies, the sponsor or a designee may follow up by telephone, fax, electronic mail, and/or a monitoring visit to obtain additional case details and outcome information (e.g. from hospital discharge summaries, consultant reports, autopsy reports) in order to perform an independent medical assessment of the reported case. A follow-up SAE form must also be completed and reported appropriately.

SUSARs will be reported to the required regulatory authorities, investigators/institutions, and ethical committees in compliance with all reporting requirements according to local regulations and good clinical practice by the sponsor and/or its designees.

Once per year, the sponsor or PCI will supply a report on the safety of trial subjects with all available relevant information concerning patient safety during the reference period to the competent supreme and the competent authorities of all other member states of the EU or EEA where the trial is being conducted. This report will also be supplied to the responsible ethics committee.

The annual safety report will be compiled according to the corresponding ICH guideline E2F „Development Safety Update Report – DSUR“

The data lock point for the patient data to be included and analyzed is the day of the approval of the clinical trial.

Detailed requirements regarding form and content are covered by the ICH Guideline E2F „Development Safety Update Report – DSUR“. The DSUR presents a comprehensive analysis of the current safety profile concerning the study drug.

The sponsor or PCI will supply the report within 60 days of one year after the reference date (data-lock point).

The data lock point is the last day of the one-year reporting period following the “Development International Birth Date” (DIBD). This date is the sponsor’s first authorization to conduct a clinical trial in any country worldwide. When the DBID is not available to the sponsor, the data lock point can be defined as the first authorization to conduct a clinical trial in the EU if an adequate explanation can be provided.

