### 5.18 Study Assessments after 3rd vaccination

See study assessments after boost vaccination above. The following derivations to the procedures described above are applied after the 3rd vaccination: no lab values on day 2 and 10; all participants will be analyzed for T cell responses on day 10, 30, 90 and 180.

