| Gastrointestinal disorders                           | Diarrhoea c                                                              | Nausea; Vomiting c |                                                                                                    |                                                |                                                            |
| Musculoskeletal and connective tissue disorders      | Arthralgia; Myalgia                                                                 |                               | Pain in extremity d                                                                     |                                                |                                                            |
| General disorders and administration site conditions | Injection site pain; Fatigue; Chills; Pyrexia; e Injection site swelling | Injection site redness        | Malaise; Injection site pruritus                                                                   |                                                |                                                            |

a. The frequency category for urticaria and angioedema was Rare.

b. Through the clinical trial safety follow-up period to 14 November 2020, acute peripheral facial paralysis (or palsy) was reported by four participants in the COVID-19 mRNA Vaccine group. Onset was Day 37 after Dose 1 (participant did not receive Dose 2) and Days 3, 9, and 48 after Dose 2. No cases of acute peripheral facial paralysis (or palsy) were reported in the placebo group.

c. Adverse reaction determined post-authorisation.

d. Refers to vaccinated arm.

e. A higher frequency of pyrexia was observed after the second dose.

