### **Thrombosis with Thrombocytopenia Syndrome (TTS)/Vaccine-induced Thrombotic Thrombocytopenia (VITT)**

TTS/VITT is caused by antibodies that recognize platelet factor 4 (PF4, also called CXCL4) bound to platelets. These antibodies are immunoglobulins (Ig) that activate platelets via low affinity platelet FcγIIa receptors (receptors on the platelet surface that bind the Fc portion of IgG).

**Urgent medical evaluation for TTS/VITT** is indicated if any of the following develops after vaccination:

- Severe headache
- Visual changes

- Abdominal pain
  - Nausea and vomiting
  - Back pain
  - Shortness of breath
  - Leg pain or swelling
- Petechiae, easy bruising, or bleeding

Many individuals are hospitalized due to the severity of their clinical condition. An exception may be an individual with isolated thrombocytopenia (without thrombosis) who can be treated with a direct oral anticoagulant (DOAC) with very close follow-up.

As an initial indicator for potential TTS, platelets will be counted in the blood sampled on day 10.

If the slightest indication for TTS/VITT arises from clinical symptoms or low platelet counts, the individual will be immediately referred to the Department for Internal Medicine V, at the University Hospital Innsbruck, to the coagulation disorder specialists.

[figure not shown]

|                                                                                                                                                                                                                                                                                                                                                                                 |
|---------------------------------------------------------------------------------------------------------------------------------------------------------------------------------------------------------------------------------------------------------------------------------------------------------------------------------------------------------------------------------|
| Presenting symptoms                                                                                                                                                                                                                                                                                                                                                      |

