## **7.3 Serious Adverse Events**

If a serious adverse event (SAE) occurs, the investigator must alert the sponsor without unjustified delay to any AE (whether causally or not) from this study that results in one of the following outcomes, or is significant for any other reason:

- death (excluding death from progressive disease)
- a life-threatening experience – refers to an event in which the subject was at risk of death at the time of the event; it does not refer to an event which hypothetically might have caused death if it were more severe
- initial hospitalization, or prolongation of existing inpatients’ hospitalization
- persistent or significant disability or incapacity
- congenital anomaly or birth defect

Additionally all Thrombosis with Thrombocytopenia Syndrome (TTS)/Vaccine-induced Thrombotic Thrombocytopenia (VITT) will be classified as serious adverse event.

Medical judgment should be exercised in deciding whether an AE/adverse drug reaction (ADR) is serious in other situations. Important AE/ADRs that are not immediately life-threatening or do not result in death or hospitalization but may jeopardize the subject or

may require intervention to prevent one of the other outcomes listed in the definition above, should also be considered serious.

Patients should be closely observed for adverse events while receiving treatment with the IMP. Further on for 12 weeks after discontinuation from study therapy in order to detect delayed toxicity. After this period, the clinical trial medical safety desk will only be alerted to serious adverse events if the investigator believes that the event may have been caused by the investigational device or by a protocol procedure.

Events not considered to be serious adverse events are hospitalizations for the:

- routine treatment or monitoring of the studied indication, not associated with any deterioration in condition
- treatment, which was elective or pre-planned, for a pre-existing condition that did not worsen
- treatment on emergency, outpatient basis for an event not fulfilling any of the definitions of serious given above and not resulting in hospital admission.

Disease progression will not be reported as AE or SAE unless the progression is unexpected in severity or early occurrence. Progressive disease will be appropriately documented on the case report form as part of the efficacy parameters.

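### Protocol sections 7.9.2, 7.3 and 7.9.1 and the visit plans give incompatible windows for reporting adverse events regardless of causality

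*Protocol*

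**What the plan says.** The protocol sets the period for adverse-event reporting in several places.

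- **Section 7.9.2, reporting sentences.** After the study vaccine is given, "all AEs and SAEs regardless of relationship to the study drug will be reported until 7 days", with some alternative end points in the same sentence (event resolved, event stable, loss to follow-up, withdrawal of consent). The next rule is: "After 8 days, investigators should report any deaths, SAEs, or other AEs of concern that are believed to be related to prior treatment".
- **Section 7.9.2, first paragraph.** All AEs go into the medical record and the adverse-event eCRF. No time limit and no causality condition is given.
- **Section 7.3.** Close observation continues after treatment: "Further on for 12 weeks after discontinuation from study therapy in order to detect delayed toxicity". Only after that period does a filter begin, when the safety desk "will only be alerted to serious adverse events if the investigator believes that the event may have been caused".
- **Section 7.9.1.** SAEs go to the sponsor within 24 hours whatever their relationship to the vaccine. No end date is given.
- **Visit plans and sections 5.8 and 5.16.** AEs and SAEs are collected at the weekly contacts to day 182 and at the day 30, 90 and 180 visits, both after the boost and after the third dose, with no causality condition.
- **Section 2.2.** The safety endpoint is the occurrence of AEs, SAEs and events of special interest, with no condition on relatedness.

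On laboratory safety, section 7.1 makes the day-10 sample the first indicator for thrombosis with thrombocytopenia: "platelets will be counted in the blood sampled on day 10". After the third dose, section 5.14 and the visit plan schedule a day-10 laboratory panel, while section 5.18 states "no lab values on day 2 and 10".

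**The concern.** A site cannot tell from this text whether a stroke on day 12 that the investigator judges unrelated has to be reported. Section 7.9.2 can be read to say no. Sections 7.3 and 7.9.1 and the visit plans say yes.

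The endpoint counts events whatever their cause. A filter on the investigator's opinion would change what is counted, and in this trial that opinion is often formed with knowledge of the vaccine received. Different relatedness thresholds for the heterologous and homologous schedules would then appear as a difference in event rates. A gap in the SAE flow would also affect the DSMB, which section 16 asks to monitor safety continuously.

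**Working it through.** The 7-day limit has no formula behind it, so the check compares the rules and works out how much follow-up each one covers.

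**Inputs.** 7 days (7.9.2); 12 weeks = 84 days (7.3); day 182 as the last weekly contact (5.7, 5.10.2, 5.15). The 12 weeks run from the end of study therapy. With a single injection I take that to be the day of the dose.

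**Share of follow-up with reporting regardless of causality.**

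1. Section 7.9.2: 7 / 182 = 3.8%. The remainder is 182 − 7 = 175 days, and 175 / 182 = 96.2%.
2. Section 7.3: 84 / 182 = 46%. The 7-day window is 7 / 84 = 8.3% of this one, or 77 days shorter.
3. Visit plans: 182 / 182 = 100%.
4. Section 7.9.1, SAEs only: no end date, so 100%.

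**Who would make the relatedness judgement.** Group B is open, and so is everyone recruited after the interim analysis (3.1, 6.8). Section 1.3 reports about 300 participants already recruited, against a total of 2124. If targets are met, (2124 − 300) / 2124 = 1824 / 2124, or about 86%, are recruited openly. For the randomized arms, section 6.8 keeps only the participants unaware of the arm, while section 11.2 says investigators are blinded too, for 90 days. Even under section 11.2, blinding could cover at most days 8 to 90 of the filtered period: 90 − 7 = 83 of 175 days (47%).

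**Whether the filter is defined.** Section 7.8 grades causality as unrelated, unlikely, probably, related or not assessable. Section 7.9.1 uses a different six-level scale. Neither section says which grades count as related for section 7.9.2, or what happens to events that cannot be assessed.

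**Whether late events are plausible on the protocol's own evidence.** Bell's palsy is a listed event of special interest (7.3). The product information reproduced in section 7.1 describes four facial-palsy cases: "Onset was Day 37 after Dose 1 (participant did not receive Dose 2) and Days 3, 9, and 48 after Dose 2". Two of the three onsets after dose 2 are later than day 7, as are three of all four. The exact 95% confidence interval for 3/4 is 19% to 99%. The day-10 platelet sample also falls after day 7.

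**What share of events could fall after day 7.** The documents give no onset distribution. As an assumption, take exponential onset cut off at day 182:

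- mean 5 days: 25% after day 7
- mean 10 days: 50%
- mean 14 days: 61%
- mean 21 days: 72%
- mean 30 days: 79%
- uniform onset: 96%

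**Third-dose laboratory tests.** Section 5.14 lists coagulation, CRP, chemistry and haematology at day 10, and the third-dose visit plan marks laboratory tests at that visit. Section 5.18 waives them. Read literally, section 5.18 removes the day-10 platelet count after the third dose, although laboratory safety after that dose is a stated objective (2.2).

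**The case against.** The strongest reply is that nothing need be lost. The 7-day sentence stands under a heading on SAE and SUSAR reporting, so it can be read as governing notification of the sponsor rather than data capture. The eCRF rule in the same section, the visit plans, and the endpoint and safety analysis carry no causality condition. The sentence after day 8, "investigators should report any deaths, SAEs, or other AEs of concern that are believed to be related", can be parsed so that relatedness qualifies only the last item, other AEs of concern; all later deaths and SAEs would then still be reported. The 7-day sentence also mixes a reporting cut-off with event follow-up, so it is not a clean stop. A low day-10 platelet count leads to immediate referral under section 7.1, and all such thrombosis cases are classed as serious, so section 7.9.1 applies to them.

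Much of this stands. A reader might infer that most events of special interest would enter the endpoint only if judged related. The documents do not support that. It requires the 7-day sentence to override every other rule, and the word most would rest on four cases of one condition. With exponential onset it needs a mean above about 10 days, which the documents do not give. The 96% describes calendar time, not a share of events.

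The reply does not remove the contradiction. Even if the 7-day sentence concerns only notification, it conflicts with sections 7.3 and 7.9.1 on that same channel: 7 days, 84 days and no limit. That the sentence allows more than one parsing is itself a reason to rewrite it.

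**Conclusion.** The protocol contradicts itself on how long AEs and SAEs are reported regardless of causality, and the passages must be reconciled. If the 7-day sentence were applied to data capture or SAE reporting, 175 of 182 follow-up days would rest on a relatedness judgement. That judgement is open-label for Group B and all post-interim recruits, and of unresolved blinding for the randomized arms. Event incidence could then be under-counted and could differ by arm.

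This consequence is conditional on a site following section 7.9.2 literally. The documents do not establish that bias will occur, its direction, or its size. The contradiction itself needs no assumption. The day-10 laboratory conflict after the third dose is a separate and equally direct inconsistency.

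**What to change.** Amend sections 7.9.2, 7.3 and 7.9.1 to state one rule that matches the visit plans and the safety endpoint:

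- Capture all SAEs and all listed events of special interest regardless of causality through the last scheduled visit (day 180/182) after each study dose.
- Record the causality assessment on one scale, and do not use it as a condition for entry.
- If the sponsor wants a short window, limit it explicitly to solicited or other non-serious AEs.
- Separate the rule for eCRF recording from the rule for notifying the sponsor, and separate both from the rule for following an event to resolution.

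Also resolve the conflict between sections 6.8 and 11.2 on investigator blinding, so that readers know under what conditions causality was judged. Separately, reconcile section 5.18 with section 5.14 and the third-dose visit plan on the day-10 laboratory panel.

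The cost is amendment wording and slightly more SAE forms. The weekly contacts and the day 30, 90 and 180 visits already ask about AEs and SAEs, so no visit is added.

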## 8. Documentation

The conduct of the study in agreement with the GCP-guidelines and the investigational plan as well as the accuracy of all data documented in the CRF are the responsibility of the investigator. All collected data of this study have to be recorded on the CRF by appropriate authorized persons. This also includes data of patients who dropped-out of the study.

The investigator records the participation on a special identification list of patients. This list gives the possibility for a later identification of the patients and contains the patient number, full name, date of birth and the date of the enrollment into the study. The identification list of patients remains in the study center after the closure of the study.

Additionally, the participation of the patient in this clinical study has to be recorded in the patient’s medical record (investigational medicinal product, number of patient or randomization, start and end of the study).

Further it has to be assured that all persons authorized for CRF entries can be identified. A list with signatures and identification codes of the persons must be archived in the ISF and TMF. Furthermore logs according to ICH E6 (e.g. Signature/Delegation/Screening/Drug Accountability log) will be implemented and maintained by the Investigator.

